#### **Serious Adverse Event**

To ensure no confusion or misunderstanding of the difference between the terms "serious" and "severe," which are not synonymous, the following note of clarification is provided:

The term "severe" is often used to describe the intensity (severity) of a specific event (as in mild, moderate, or severe myocardial infarction); the event itself, however, may be of relatively minor medical significance (such as severe headache).

This is not the same as "serious," which is based on patient/event outcome or action criteria usually associated with events that pose a threat to a patient's life or functioning.

Seriousness (not severity) serves as a guide for defining regulatory reporting obligations.

After reviewing the various regulatory and other definitions in use or under discussion elsewhere, the following definition is believed to encompass the spirit and meaning of them all:

*A serious adverse event (experience) or reaction is any untoward medical occurrence that at any dose:*

- results in death;
- is life-threatening;
- requires inpatient hospitalization or prolongation of existing hospitalization;
- results in persistent or significant disability/incapacity; or
- is a congenital anomaly/birth defect.

The term "life-threatening" in the definition of "serious" refers to an event in which the patient was at risk of death at the time of the event; it does not refer to an event which hypothetically might have caused death if it were more severe.

Medical and scientific judgment should be exercised in deciding whether expedited reporting is appropriate in other situations, such as important medical events that may not be immediately life-threatening or result in death or hospitalization but may jeopardize the patient or may require intervention to prevent one of the other outcomes listed in the definition above. These should also usually be considered serious.

Examples of such events are intensive treatment in an emergency room or at home for allergic bronchospasm; blood dyscrasias or convulsions that do not result in hospitalization; or development of drug dependency or drug abuse.

All unanticipated problems/adverse events/serious adverse events will be recorded on the case report form (CRF) and in the source documents at the site of testing. A log for all unanticipated problems/adverse events/serious adverse events occurring in the study will be kept. The details of any unanticipated problems/adverse events/serious adverse events at each study visit, using the protocol-defined terminology, will be recorded.

The PI and or RC will educate the participants about unanticipated problems/adverse events/serious adverse events as well as the importance of reporting them to the study coordinator at study visits.

Anyone within the research team who becomes aware of unanticipated problems/adverse events/serious adverse events will report this to the PI. The PI will assess the unanticipated problems/adverse events/serious adverse event and provide the research participant with appropriate medical care as applicable. The PI will report to the REB within 7 days only the local adverse events/serious adverse events that are deemed to be unanticipated problems.

The monitoring of these unanticipated problems/adverse events/serious adverse will be made in accordance with the Ottawa Health Sciences Network Research Ethics Board's SOP 404.001 Ongoing REB Review Activities including the SOP 404 Adverse Event Reporting Requirements addendum.

**Risks of Insurability**

All study staff members will take all reasonable steps to ensure participant research information is kept confidential. Should someone not involved in the research find out about the identity(ies) of individual participants, there is a possibility that this could affect one's insurability under certain policies of insurance, depending on the exclusions in such policies.

**Benefits of Participant Participation**

Participants may not receive any direct benefit from their participation in this study. Upon completion of the study, participants will receive a summary of their fitness measurements.

**Withdrawal Criteria**

Participants have the right to withdraw from the study at any point in time. Staff conducting the study has the right to withdraw participants from this study for any of the following reasons:

- The investigator feels it is in the participant's best interest.
- Participant needs medication/treatment that would interfere with the study.
- Participant does not follow the study staff's instructions.

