## **Sample Size**

The sample is sufficient to test the two primary research hypotheses simultaneously using repeated measures mixed models analyses (group: (1) moderate-intensity continuous exercise training, (2) high-intensity interval training; time: (1) baseline, (2) 12 weeks follow-up). A sample size of 48 participants (24 per group) is needed to detect a difference of 67 m on the 6-minute walk test (6MWT) between the two groups at a two-sided 0.025 significance level with 80% power, assuming that the standard deviation (SD) of the response variable is 150 m. The minimal clinically important difference (MCID) for the 6MWT is estimated to be 54-80 m using both distributional and discriminative methods. A sample size of 98 participants (49 per group) is needed to detect a difference of 5 points in the physical component score (PCS) between the 2 groups on the Short Form-36 questionnaire (SF-36) with a two-sided 5% significance level and 80% power, assuming the SD of the response variable is 10 points.

The MCID in quality of life as measured by the PCS of the SF-36 is a change score of 5. We will use the larger sample of the two as the study size to ensure we have adequate power for both hypothesis tests. We will use an ‘intention to treat’ strategy in our primary analysis, however we adjusted our sample size upward to account for a planned 10% loss to follow-up to allow a secondary analysis using only participants with complete outcome data. We therefore plan to randomize 108 participants in the trial.

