**Secondary Measures**

Secondary measures will include: 1) exercise adherence measured by accelerometer (and verified using a 7-day FIIT log; 2) activity status measured by the Duke Activity Status Index (DASI); 3) atrial fibrillation specific quality of life measured by the University of Toronto Atrial Fibrillation Severity Scale (AFSS); 4) symptom burden measured by the Canadian Cardiovascular Society Severity of Atrial Fibrillation (CCS-SAF) scale; 5) self-reported symptom frequency and severity measured by the 7-day symptom diary; 6) anxiety and depressive symptoms measured by the Hospital Anxiety and Depression Scale (HADS); 7) insomnia severity measured by the Insomnia Severity Index; 8) sleep apnea risk measured by the STOP-BANG Sleep Apnea Questionnaire; and 9) self reported sleep patterns measured by the 7-day sleep diary.

1. Exercise adherence: will be measured directly and by self-report. The Actigraph GT3X accelerometer will be used for direct measurement and worn over the right hip for a 7-day recording period. The activity monitor provides physical activity measurements including activity counts, intensity levels and energy expenditure. A FITT (frequency, intensity, time, type) log will be used to gather weekly self-reported data of exercise training over the course of the 12 weeks of study

participation. Minutes of moderate and vigorous intensity exercise training per week will be summed and used to assess moderate-intensity continuous exercise training and high-intensity interval training adherence.

2. Activity status: will be measured using the Duke Activity Status Index (DASI), a self-administered questionnaire comprising 12 questions that determines a persons' functional capacity. Higher scores represent greater functional capacity. The DASI is a validated measure that is highly correlated with objective measures (e.g. VO2peak).

3. Atrial fibrillation Specific Quality of life: will be measured using the University of Toronto Atrial Fibrillation Severity Scale (AFSS). The AFSS is a disease-specific quality of life measure used to capture subjective and objective ratings of disease burden in patients with atrial fibrillation. It consists of 19 items and assesses atrial fibrillation burden (4 items), health care utilization (4 items) and symptom severity (7 items). The AFSS has been tested according to standardized psychometric parameters of content validity, reliability and variability.

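### Staff may withdraw participants from the whole study for non-compliance or other treatment, with no provision for week-12 assessment; this can tie missing primary outcomes to adherence and undermines the intention-to-treat strategy

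*Protocol*

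**What the plan says.** Withdrawal Criteria in the protocol: "Staff conducting the study has the right to withdraw participants from this study for any of the following reasons". Three reasons follow. One is "Participant does not follow the study staff's instructions", with no definition of instructions and no threshold. Another is the need for a medication or treatment that would conflict with the study. The third is the investigator's view of the participant's best interest. The object of withdrawal is the study, not the training programme.

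Sample Size: "We will use an ‘intention to treat’ strategy in our primary analysis". The sample was then enlarged to "account for a planned 10% loss to follow-up to allow a secondary analysis using only participants with complete outcome data", and the section ends: "We therefore plan to randomize 108 participants in the trial".

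Sample Size and Analyses of Results name repeated measures mixed models, with time defined as baseline and 12 weeks. The schedule table shows the 6MWT and the questionnaires at baseline, at week 12 and at the later follow-up visits from week 26, with none in between. Secondary Measures lists "exercise adherence measured by accelerometer" as its first item.

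No section says whether a participant withdrawn by staff is still invited to the week-12 visit.

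**The concern.** Intention to treat needs outcomes from everyone randomised, whatever they did afterwards. The withdrawal rule allows staff to end a person's participation because of what happened after randomisation: not following instructions, or coming to need another treatment. If withdrawal also ends outcome collection, the missing week-12 values are related to adherence or tolerance, and these may differ between the two training arms.

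The protocol itself expects such a difference. Its Background suggests that interval training may improve adherence, and its Hypotheses predict better adherence in that arm. The Background also faults earlier studies for high withdrawal rates.

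An analysis plan cannot repair this afterwards. It can choose a missing-data method, but it cannot restore a walk test or questionnaire that was never done. The accelerometer adherence outcome is exposed in the same way, because its post-intervention recording falls at week 12.

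**Working it through.** **1. The plan's own figure.** The larger sample before inflation is 98 (49 per group).
- 98 × 1.10 = 107.8, so 108.
- 98 / 0.90 = 108.9, so 109.

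The stated 108 (54 per arm) reproduces by the first route. The 10% allowance covers loss of numbers. It does not protect against loss that depends on adherence.

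**2. What the mixed model does with a withdrawn participant.** With two time points, a participant without week 12 supplies only a baseline value. The model in effect gives that person the week-12 outcome expected from baseline and arm among those who stayed. This is unbiased only if, given baseline and arm, those removed would have done as well as those kept. The trial data cannot test that.

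**3. Bias formula.** In one arm, let p be the share removed and g the week-12 gap, at equal baseline, between those kept and those removed. If those kept average k, then:
- mean of all randomised = (1 − p)k + p(k − g) = k − pg
- kept mean minus full mean = pg
- bias in the HIIT minus MICE difference = pH·gH − pM·gM

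A positive value favours HIIT.

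**4. Inputs.** The protocol gives no p and no g, so all values below are assumed. The yardsticks are its target differences of 67 m (6MWT) and 5 points (PCS).

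| Removed, HIIT / MICE | Gap in both arms | Bias |
|---|---|---|
| 10% / 10% | 60 m | 6 − 6 = 0 m |
| 15% / 5% | 60 m | 9 − 3 = +6 m |
| 5% / 15% | 60 m | 3 − 9 = −6 m |
| 25% / 10% | 60 m | 15 − 6 = +9 m |
| 10% / 25% | 60 m | 6 − 15 = −9 m |
| 15% / 5% | 2.5 PCS points | 0.375 − 0.125 = +0.25 |
| 15% / 5% | 5 PCS points | 0.75 − 0.25 = +0.5 |
| 20% / 5% | 10 PCS points | 2.0 − 0.5 = +1.5 |

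Reversing the rates reverses the sign in every row with unequal rates.

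**5. Reading the table.** The 15% / 5% rows average 10%, which equals the planned loss. Here 6 m is 6/67 = 9% of the 6MWT target, and 0.5 points is 0.5/5 = 10% of the PCS target. The 25% / 10% rows average 17.5%, above the planned loss, and give 9/67 = 13%. The last row gives 1.5/5 = 30%, but needs both a large gap and a fourfold difference in removal.

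**The case against.** The strongest objection is that the text grants a discretionary right and does not order removal. Instructions are not defined as attendance at training and could equally mean test or safety instructions. The section is silent on outcome collection after withdrawal, and the consent form, which was not available here, may address it. Non-adherers whom staff do not withdraw remain in follow-up. Everyone randomised can still be analysed as assigned. The plan also allows for 10% loss and keeps the complete-data analysis secondary. Missing-data methods commonly belong to an SAP, which is not at hand.

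Much of this stands, and it rules out a stronger reading. A reader might infer that the rule removes all non-adherers, turns the estimate into an effect among compliers and defeats intention to treat. That would require every non-adherer to be withdrawn and never assessed, which the protocol does not say. A reader might also infer a bias in favour of HIIT. The protocol's own expectation of better adherence with HIIT points, if anything, the other way, and equal rates and gaps give no bias. Nor does the protocol say who decides on withdrawal or whether that person knows the arm; only those supervising the sessions necessarily do.

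The effect on adherence is also partial. Secondary Measures describes weekly self-reported exercise logs over the 12 weeks, so some data before withdrawal would exist. The post-intervention accelerometer week is what would be lost.

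The objection does not answer the central gap: a stated rule permits withdrawal from the whole study on grounds linked to adherence or tolerance, and nothing keeps those people in the week-12 assessment.

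**Conclusion.** The concern holds as a conflict between the withdrawal rule and the declared primary strategy. The rule can make the week-12 6MWT and PCS missing in relation to post-randomisation adherence or tolerance. It weakens the intention-to-treat analysis; it does not defeat it.

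The size cannot be fixed from the protocol. If removals match the planned 10% on average, split 15% to 5%, and the assumed gap is 60 m, the bias is about 6 m in either direction. It reaches 9 m at 25% versus 10%, and is zero when rates and gaps are equal. These are illustrations, not predictions. They assume that withdrawn participants have no week-12 data and that the gap is not explained by baseline.

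The bias is modest in most of these cases. The case for acting is that the remedy is cheap and that outcomes not collected cannot be recovered.

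**What to change.** Reconcile Withdrawal Criteria with Sample Size by amendment:

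- Separate two events: discontinuing study training, and withdrawing from follow-up. The grounds for discontinuing training stay with the investigators, and no rule on that is proposed here.
- Do not use non-compliance or the need for other treatment as a ground to end outcome collection.
- Seek the week-12 6MWT and SF-36 from every randomised participant unless consent is withdrawn.
- Analyse all participants by assigned arm, including data obtained after training stopped.

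The cost is a short amendment and some effort to bring back participants who have stopped training. The week-12 visit is already in the schedule, so no new procedure is needed. The change helps only those whose week-12 assessment is still to come, so it should be made early.

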**Confidentiality/Privacy**

All Personal Health Information (PHI) and Personal Identifying Information (PII) will be kept confidential, unless release is required by law. Release of PHI/PII information will only be allowed if it is legally required by law. For audit purposes only, representatives of the Ottawa Health Sciences Network Research Ethics Board (OHSN-REB) and the University of Ottawa Heart Institute may review participants' records under the supervision of [name] staff.

Results of research studies should be shared, to ensure participants are always provided with the best possible care. Therefore, results from this study may be presented at scientific conferences and/or published in journals but participants' will not be identifiable in any publications or presentations.

All participants will be assigned a study ID number once informed consent is obtained. The study ID will serve as the only identifier used on all study related documents. Informed consent will occur at the time of recruitment once verification of eligibility has been completed. The master list will be maintained by study staff and stored in a separate file from the coded study dataset on a password protected computer. The master list will be in a password protected file stored separately from all other study files; the master file will be password protected and only individuals directly involved with the study (e.g., PI or designate) will have access to this file. The participant identifiers to be stored in the master list include full name and contact information (e.g., phone number, email, address). The University of Ottawa Heart Institute and the Health Sciences Network Research Ethics Board (OHSN-REB) will have access to the records for audit purposes.

A separate database will be kept that contains study ID numbers along with personal identifiers. The database containing descriptive information (e.g., height, weight, etc.) will only have study ID numbers as identifiers. Case Report forms will only have study ID numbers used as identifiers, all other personal information (e.g., name) will not be collected on these forms. Participants will be reminded

not to write their name on any forms. Please refer to the Case Report Form (CRF) for personal health information to be collected.

No identifying information will leave the University of Ottawa Heart Institute. All information that leaves the University of Ottawa Heart Institute will be coded with an independent study number that will be used throughout the study on all of the study records. The Master List which links participants' name and the independent study number will only be accessible by [name] and/or her staff. The link and study files will be stored separately and securely.

### **Record Keeping/Document Management**

The research staff will collect the case report forms and questionnaires. Both paper and electronic records will be provided to [name] and her staff. All paper records will be stored in a locked filing cabinet and office. All electronic records, including the Master List, will be stored on a secure internal hospital server and password protected, only accessible by [name] and/or her staff. No identifiable information will be stored on any mobile devices (laptops, USB keys, CDs, DVDs, etc.). Research files will be kept for a period of 10 years after the study has been completed, as required by law. At the end of the retention period, all paper records will be disposed of in confidential waste for shredding and all electronic records will be securely deleted.

### **Data Handling**

All data will only be accessible by [name] and/or co-investigators or collaborators or staff.
